**Figure 1 F1:**
[figure not shown]
Study arm description.

The sample size is calculated using the formula:

S = (zα + zβ) ∧ 2 ^*^ (C^*^(1–C) + I^*^(1–I)) / (C–I) ∧ 2, where C represents the expected proportion in the control arm and I represents the expected proportion of the intervention arms.

Participants will be screened based on their baseline self-efficacy score, and TB treatment facilities will be regarded as clusters. During the recruitment phase, the matching of average self-efficacy scores between the intervention and control clusters will be assessed. Recruitment within each cluster will continue until the required sample size per cluster is achieved. Eligible participants will be enrolled sequentially from the health centres within the designated selected TU.

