## Primary objectives

To adapt and evaluate the self-efficacy-based intervention compared with the standard of care on the following outcomes:
• Primary outcomes: *improved TB treatment self-efficacy*.• Secondary outcomes: *(i) improved medication adherence (ii) reduced TB-related stigma and (iii) improved infection control self-management practices*.To evaluate the efficacy of a self-efficacy-based intervention, compared with the standard of care, on secondary outcomes among caregivers: *improved caregivers' self-efficacy, decreased TB-related stigma, and improved infection control self-management practices*.To assess the acceptability level among patients, caregivers, and health care providers.

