## Overall design

A hybrid mixed-method implementation design will be employed to evaluate the implementation acceptability and preliminary efficacy of delivering a self-efficacy-based intervention by front-line healthcare staff, family caregivers, and patient champions. The intervention aims to enhance treatment self-efficacy, mental health, and self-management practices related to infection control among individuals with TB and caregivers.

## Design for primary objective 1

A self-efficacy-based intervention manual and standard operating procedures were developed by adapting the findings from formative research conducted among individuals with TB, caregivers, and front-line healthcare staff. The PRODUCES framework (Problem, Objective and Design, End-Users, Co-creators, Evaluation, and Scalability) was used to guide the design and development of this implementation research study (10).

The self-efficacy drive intervention manual and standard operating procedures (SOPs) will be further adapted to align with the workflow of government TB care delivery systems at the proposed study sites (11).

## Design for primary objective 2

A two-arm, non-randomized cluster intervention study will be conducted to achieve this objective. The study population will include

Adult drug-sensitive (DS) TB patients (> 18 years) who have initiated TB treatment.Patients with low treatment self-efficacy (self-efficacy score of < 30 on the chronic diseases self–efficacy scale) (12).Adult drug-resistant (DR)-TB patients on a shorter treatment regimen.Caregivers of patients who meet criteria 1–3 above.

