## Analysis of study outcomes data

The following standardized tools and scales will be used for the present study at three different time points: 1. Baseline (Initial phase of treatment), 2. Midline (3rd month of treatment), and 3. Endline (6th month of treatment), and on average, it takes 40–50 min to complete all the scales.

Self-Efficacy for Managing Chronic Disease 6-item Scale (12).Caregivers' Self-Efficacy Scale (CSES-8) (14).TB Stigma Scale (15).Patient Health Questionnaire-9 (16).AUDIT-C scale for alcohol dependence (17).Airborne Infection Control (AIC) practices Survey Questionnaire (18).TB Medication adherence and Treatment outcomes (assessed at midline and endline).

All analyses will be conducted following an intent-to-treat (ITT) approach. Continuous outcomes, including self-efficacy score and other secondary outcomes (e.g., PHQ-9 scores, AUDIT-C scores, and TB stigma scores), will be analyzed using linear mixed models. Fixed effects in the model include:

Treatment arm (0 = usual care; 1 = self-efficacy-based intervention).Time (0 = baseline, 1 = 3 months post-baseline; 2 = 6 months post-baseline).Interaction terms between the treatment arm and time (Treatment × Time interaction term).

This modeling approach will allow estimation of mean differences in change scores between study arms with 95% confidence intervals (CIs). Cohen's *D* will be calculated to estimate the effect size. Covariates showing meaningful baseline differences will be adjusted for in the models. For non-normally distributed continuous outcomes, generalized linear mixed effects models with the appropriate link functions will be employed.

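### One self-efficacy score both selects patients and serves as the time-0 primary outcome, so regression to the mean enters the within-arm change and may not cancel between non-randomised arms

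*Protocol article*

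**What the plan says.** All references are to the protocol article.

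- **Eligibility** (Design for primary objective 2). The study population includes patients with a "self-efficacy score of < 30 on the chronic diseases" self-efficacy scale, citing reference 12. The list does not say whether every criterion must be met. The Implementation section describes the evaluated patients as having low treatment self-efficacy, which suggests that the cut applies to all of them.
- **Screening** (Sample size, text after Figure 1). "Participants will be screened based on their baseline self-efficacy score, and TB treatment facilities will be regarded as clusters". No separate screening measurement is described.
- **Primary outcome** (Primary objectives). "improved TB treatment self-efficacy". The instrument listed under Analysis of study outcomes data is the six-item chronic-disease self-efficacy scale, again with reference 12.
- **Model** (Analysis of study outcomes data). A linear mixed model with arm, time and their interaction, in which baseline is time 0. "This modeling approach will allow estimation of mean differences in change scores between study arms".
- **Allocation**. Two arms of non-randomised clusters, five per arm.
- **Safeguards**. During recruitment "the matching of average self-efficacy scores between the intervention and control clusters will be assessed", with no tolerance and no action stated. Covariates that differ meaningfully at baseline are to be adjusted for.

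**The concern.** A patient can fall below 30 because self-efficacy is truly low or because that day's reading was low. The second kind tends to score higher next time with no intervention. When the reading that admits the patient is also the starting point for change, this rebound becomes part of the within-arm improvement in the primary outcome.

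In a randomised comparison the rebound would be equal in expectation and would drop out of the arm-by-time term. Here it drops out only if the two sets of facilities draw on patients with similar score distributions and measure them equally well. If they do not, the primary contrast carries a bias whose sign depends on which arm has the higher source mean or the noisier measurement. With only one pre-treatment reading, it cannot later be separated from a real effect.

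**Working it through.** **The plan's own figures.** The plan gives no figure on this point. Its 166 per arm reproduces: (1.960 + 0.842)² × (0.50 × 0.50 + 0.35 × 0.65) / 0.15² = 166.57. That figure has no bearing on the rebound.

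**Inputs from the document.** Cut-off 30; target d > 0.3; 500 patients in two arms, so 250 per arm; design effect 1.5.

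**Assumed inputs, not in the document.** Normally distributed screening scores with SD 12; source means 30 in one arm and 34 in the other; reliability ρ from 0.5 to 0.8; stable true score; independent errors; no intervention effect.

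**Formulas.** With a = (30 − mean)/SD and λ = φ(a)/Φ(a):
- enrolled mean = mean − SD × λ
- expected rebound = (1 − ρ) × SD × λ
- enrolled SD = SD × √(1 − aλ − λ²)

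**Source mean 30.** a = 0 and λ = 0.3989/0.5 = 0.798. Enrolled mean 30 − 12 × 0.798 = 20.4; enrolled SD 7.2.

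**Source mean 34.** a = −0.333 and λ = 0.3774/0.3694 = 1.021. Enrolled mean 34 − 12 × 1.021 = 21.7; enrolled SD 6.5.

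The pooled enrolled SD is √((7.23² + 6.54²)/2) = 6.9.

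| ρ | Rebound, mean 30 | Rebound, mean 34 | Difference (bias) | As d (÷ 6.9) |
|---|---|---|---|---|
| 0.5 | 4.79 | 6.13 | 1.34 | 0.19 |
| 0.6 | 3.83 | 4.90 | 1.07 | 0.16 |
| 0.7 | 2.87 | 3.68 | 0.81 | 0.12 |
| 0.8 | 1.91 | 2.45 | 0.54 | 0.08 |

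**Equal arms.** With the same mean, SD and reliability in both arms, the difference is zero by the formula; simulation with 2 million screened per arm gave −0.0003 SD.

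**Sensitivity.**
- If 60% of screened patients fall below the cut in one arm and 40% in the other, the bias is 0.27, 0.16 and 0.05 enrolled-baseline SD at ρ = 0.5, 0.7 and 0.9.
- With equal means of 30 but reliability 0.6 in one arm and 0.8 in the other, it is (0.8 − 0.6) × 12 × 0.798 = 1.91 points, or 1.91/7.23 = 0.26 SD. The source and enrolled means are then the same in both arms, so no comparison of averages would show it.

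**What the matching check would see in the 30 v 34 case.** The 4-point source gap appears among enrolled patients as 21.74 − 20.43 = 1.3 points, or 0.19 enrolled SD. Its standard error is about 6.9 × √(2 × 1.5/250) = 0.76, so the gap is about 1.7 standard errors.

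**Re-measured baseline.** Under the same assumptions, change from an independent second reading taken after selection is 0.00 (± 0.02 in simulation) in every setting.

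**The case against.** The strongest reply is that success is defined by comparison with the control arm, not by pre-post change, and equal rebound cancels in that comparison. All sites lie in three districts of one state under one programme, and nothing in the document shows that their patients differ. This stands. A reader might infer that the rebound does differ between arms; the document supports only that it may.

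A reader might also infer that every change score is affected. Selection is on patient self-efficacy alone. Stigma, depression, alcohol and caregiver scores are touched only through their correlation with it, and adherence, assessed only at midline and endline, has no baseline value to change from.

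A third tempting reading is that the matching check cannot detect the problem. The document does not say that the check uses enrolled patients only. Even if it does, the worked example leaves a visible gap of 1.3 points, about as large as the bias or larger at every reliability shown. Truncation weakens the signal without removing it. Covariate adjustment is a further safeguard and may help where covariates explain a source difference. Neither safeguard is strong if it relies on enrolled scores: the gap is compressed, no tolerance is given, and unequal reliability leaves no gap in means.

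Finally, a second reading removes only short-term error. Slower fluctuation after diagnosis could persist at a re-test and still regress by months 3 and 6. This limits the fix but does not defeat it.

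**Conclusion.** The point holds in a limited form. As written, one reading on one scale both admits the patient and starts the change in the primary outcome, so within-arm change in self-efficacy includes regression to the mean. The between-arm contrast may be biased, in either direction, if source-population scores or measurement reliability differ between arms.

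The size cannot be fixed from the document, which gives no score distribution or reliability. In the 30 v 34 scenario the bias is about 0.5 to 1.3 points (d of about 0.08 to 0.2), below the 0.3 target in each case but a substantial part of it. The other scenarios shown reach 0.27, and with equal source populations and reliability the bias is zero. Confidence is high in the mechanism and low in any particular size. The case for a change rests on its small cost and on the fact that it must be made before recruitment.

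**What to change.** 1. Use the screening score for eligibility only. Repeat the six items after enrolment and before the first session, and use that second value as time 0 in the primary-outcome model and in self-efficacy change scores. Apply the same procedure and timing in both arms.
2. Log the scores of all screened patients by facility, including those at 30 or above, and assess cluster matching on those unselected means.
3. State in the eligibility list whether the cut at 30 applies to every patient.

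Cost: six extra items, a screening log and possibly one more short contact, since the article describes no screening visit separate from the baseline interview. Apparent within-arm gains will be smaller. Some regression may remain if scores fluctuate slowly after diagnosis.

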## Intervention description

### Self-efficacy driven intervention

The intervention will comprise the following core components: motivational approach, behavioral skills-building and adaptations, self-management skills, and supportive care for patients and their caregivers. Each component will include specific, structured activities aligned with the principles of self-efficacy.

The intervention will be implemented through a combination of individual and group sessions that incorporate elements of cognitive behavioral therapy, individual counseling, and group therapy. The content of these sessions will include elements such as motivation, goal setting, psychoeducation, problem-solving, mind diversions, normalization, behavioral activation, and cognitive coping.

The intervention will be synchronized with the NTEP treatment schedule and integrated within the routine care practices. The intervention will be delivered across 10–12 structured sessions, beginning at treatment initiation and continuing through completion.

Session frequency and duration will vary according to the treatment phase:

Initial phase (1st month): brief sessions of 10–15 min, delivered weekly.Intensive phase: sessions extended to 20–40 min, delivered fortnightly.Continuation/final phase: sessions maintained at 20–40 min, delivered monthly.

Interventions will take place at the TUs or local treatment centres where patients receive their care, with the option of home-based delivery for participants who prefer it. Each component of the intervention (Figure 2) will be administered by trained counselors by following a co-creation and adaptation framework (11, 13).

**Figure 2 F2:**
[figure not shown]
Components of an integrated self-efficacy driven intervention for individuals with TB and caregivers.

### Enhanced standard of care arm intervention

In accordance with the Declaration of Helsinki, the participants in the control arms of randomized trials, will receive highest available standard of care. Participants in the intervention arm will receive a brief counselling and motivational discussion in addition to the routine care provided by a frontline healthcare staff in TB health facilities.

Information, Education, and Communication (IEC) materials will be distributed to patients and caregivers, covering topics such as nutrition, risk behavior reduction, and infection control practices. Patients diagnosed with alcohol use disorder or depression will be referred to government psychiatric services for further evaluation, care, and follow-up.

## Evaluation and analysis: quantitative component

Healthcare centres within the selected TUs at the study sites will serve as recruitment points for eligible individuals on DS TB or DR TB treatment with oral shorter regimens, along with their caregivers.

Data collection will occur at three time points: treatment initiation, midpoint, and completion. At each stage, trained study personnel will administer the standardized questionnaires to participants in both the control and intervention arms. These questionnaires will cover a variety of topics, including patient self-efficacy related to TB treatment, medication adherence and infection control practices, TB-related stigma, depression, caregivers' self-efficacy, and stigma. Additionally, the air quality assessments will be conducted at the baseline and midpoint of treatment in the homes of selected and consenting patients using aerosol samplers to evaluate infection control conditions.

## Analysis of study outcomes data

The following standardized tools and scales will be used for the present study at three different time points: 1. Baseline (Initial phase of treatment), 2. Midline (3rd month of treatment), and 3. Endline (6th month of treatment), and on average, it takes 40–50 min to complete all the scales.

Self-Efficacy for Managing Chronic Disease 6-item Scale (12).Caregivers' Self-Efficacy Scale (CSES-8) (14).TB Stigma Scale (15).Patient Health Questionnaire-9 (16).AUDIT-C scale for alcohol dependence (17).Airborne Infection Control (AIC) practices Survey Questionnaire (18).TB Medication adherence and Treatment outcomes (assessed at midline and endline).

All analyses will be conducted following an intent-to-treat (ITT) approach. Continuous outcomes, including self-efficacy score and other secondary outcomes (e.g., PHQ-9 scores, AUDIT-C scores, and TB stigma scores), will be analyzed using linear mixed models. Fixed effects in the model include:

Treatment arm (0 = usual care; 1 = self-efficacy-based intervention).Time (0 = baseline, 1 = 3 months post-baseline; 2 = 6 months post-baseline).Interaction terms between the treatment arm and time (Treatment × Time interaction term).

This modeling approach will allow estimation of mean differences in change scores between study arms with 95% confidence intervals (CIs). Cohen's *D* will be calculated to estimate the effect size. Covariates showing meaningful baseline differences will be adjusted for in the models. For non-normally distributed continuous outcomes, generalized linear mixed effects models with the appropriate link functions will be employed.

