## Sample size

We estimated that our proposed intervention would reduce the proportion of individuals with poor self-efficacy from 50 to 35%, corresponding to an absolute difference of 15%. A sample size of 166 TB patients per arm (332 in total) was calculated assuming an average cluster size of 50, a significance level of α = 5%, β = 20% and a power 1–β = 80%.

Considering an average cluster size of 50, yielding a design effect of 1.5, we predict that we would require 500 participants, with five clusters in the control arm and five in the intervention arm. Accounting for an anticipated 10% dropout rate, we plan to screen and include approximately 547 participants overall. Arm wise sample size has been explained in Figure 1.

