## Analysis of intervention uptake and completion

To identify the predictors of intervention completion, a logistic regression model (logit model) with a binary outcome will be estimated, where:

Outcome variable: completion status (1 = completer; 0 = non-completer).Predictor variables: demographic, clinical, and socio-economic factors.

Results will be reported as odds ratios (ORs) with corresponding 95% confidence intervals.

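### Allocation is by facility and the sample size pays for clustering, but the stated primary model names no facility random effect or other cluster adjustment

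*Protocol article*

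**What the plan says.** Under the design for primary objective 2, the protocol article states: "A two-arm, non-randomized cluster intervention study will be conducted to achieve this objective". Below the sample size formula it adds that "TB treatment facilities will be regarded as clusters". The Sample size section plans five such clusters per arm with an average of 50 patients each, and applies a design effect of 1.5. No ICC is given.

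In the section on analysis of study outcomes data, continuous outcomes, including the self-efficacy score, "will be analyzed using linear mixed models. Fixed effects in the model include" treatment arm (coded 0/1), time (coded 0/1/2) and "Interaction terms between the treatment arm and time (Treatment × Time interaction term". The section says that this model will yield between-arm differences in change scores with 95% confidence intervals. Two further elements are given: adjustment for covariates that differ at baseline, and generalised linear mixed models for non-normal outcomes. Neither the facility nor any other allowance for clustering is mentioned. No random effect of any kind is described.

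For intervention completion, "a logistic regression model (logit model) with a binary outcome will be estimated" with demographic, clinical and socio-economic predictors. Facility is not mentioned there either.

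**The concern.** The design and the sample size treat the facility as the unit of allocation, while the stated analysis does not refer to it. With three visits per patient, a patient random intercept is enough to make a model mixed. It handles repeated measurements on one person, but not the shared course of patients treated at the same facility.

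Adding a facility intercept alone would not settle the matter. The effect of interest is the arm-by-time interaction, which is a difference in change. A facility effect that is constant over time cancels from a change. The variation that reaches this contrast is facility-by-visit variation: some facilities' patients improve more than others' for reasons unrelated to arm. The intervention sessions take place at the treatment units and include group sessions, so such variation is plausible.

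At stake are confidence intervals that are too narrow and a p < 0.05 criterion (set in the hypothesis section) that is met too often under no effect. With only ten facilities, the reference distribution matters as well as the variance.

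**Working it through.** **1. The plan's own figure.** Inputs from the Sample size section: "reduce the proportion of individuals with poor self-efficacy from 50 to 35" per cent, with "a significance level of α = 5%, β = 20% and a power 1–β = 80" per cent. The article's formula, with z = 1.96 and 0.84:

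S = (1.96 + 0.84)² × (0.50 × 0.50 + 0.35 × 0.65) / 0.15² = 7.84 × 0.4775 / 0.0225 = 166.4

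This agrees with "A sample size of 166 TB patients per arm (332 in total") and shows that alpha is two-sided (one-sided alpha would give 131). Then 332 × 1.5 = 498, or about 500 = 10 × 50. The sample size therefore does pay for clustering.

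**2. Implied ICC.** From 1 + (50 − 1) × ICC = 1.5, ICC = 0.5/49 = 0.0102.

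**3. Type I error if facility is ignored and the design effect (DE) of 1.5 applies to the tested contrast.** The standard error is too small by √1.5 = 1.22, so

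2 × [1 − Φ(1.96/√1.5)] = 2 × [1 − Φ(1.600)] = 0.1095

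A simulation of 10 clusters of 50 (8,000 null trials) gave 0.110. Under the same condition, assumed ICCs of 0.005, 0.02 and 0.05 give 0.079, 0.164 and 0.291.

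**4. The contrast that the model actually tests.** The 1.5 was set for a proportion at one time, whereas the model tests change in a score. Let ρ be the ICC at one visit, c the correlation of facility effects between visits and r the correlation of individual effects between visits. For a change between two visits:

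- facility variance = 2ρ(1 − c)
- individual variance = 2(1 − ρ)(1 − r)
- ICC of change = facility variance / (facility + individual variance)
- DE = 1 + 49 × ICC of change

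The article gives neither c nor r, so both are assumptions. At ρ = 0.0102 and r = 0.5:

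| c | ICC of change | DE | Type I error, formula | Simulated, facility ignored | Simulated, t on facility means (8 df) |
|---|---|---|---|---|---|
| 1 | 0 | 1.00 | 0.050 | 0.051 | 0.052 |
| 0.8 | 0.0041 | 1.20 | 0.074 | 0.076 | 0.048 |
| 0.5 | 0.0102 | 1.50 | 0.110 | 0.111 | 0.051 |
| 0 | 0.0202 | 1.99 | 0.165 | 0.168 | 0.054 |

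Example, c = 0.8: 2 × 0.0102 × 0.2 = 0.0041; 2 × 0.9898 × 0.5 = 0.9898; ratio 0.0041; DE 1 + 49 × 0.0041 = 1.20.

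When c = r, the ICC of change equals ρ and the design effect of 1.5 carries over unchanged. With r = 0.7 the errors at c = 1, 0.8, 0.5 and 0 are 0.05, 0.090, 0.147 and 0.227.

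The simulation used a patient-level test of change between two visits, not a fitted three-visit mixed model. With complete, balanced data, a patient random-intercept model estimates the same difference in mean change. Its residual variance absorbs both variance components above, so the same formula applies to a close approximation.

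**5. Degrees of freedom.** Ten facilities in two arms leave 8 between-facility degrees of freedom. The 97.5% t quantile is 2.306, and 2.306/1.96 = 1.18. In simulation, analysing facility means but referring the result to 1.96 still rejected in about 8 to 9% of null trials.

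**The case against.** The strongest reply is that silence is not exclusion. The article lists fixed effects, and a facility term would normally be random, so its absence from that list proves little. The patient effect is not listed either, although a mixed model needs some random effect. The document is a condensed article, the full protocol and SAP are not shown, and random-effects structure and degrees-of-freedom methods often sit there. The authors plainly know about clustering, since they inflated for it.

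This stands against the stronger reading that a reader might infer: that the plan has decided to ignore facilities, and that its type I error is therefore double the nominal level. The text does not exclude a facility random effect. The doubling is one point in a range that includes no inflation, because a facility effect that is stable over time drops out of the arm-by-time contrast. The design effect of 1.5 was derived for a proportion at a single time, and nothing in the article says that it carries over to change in a continuous score.

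The reply does not dispose of the point. The article goes beyond naming a model class: it itemises terms and their coding, and names the contrast that will yield the confidence intervals. A default patient-level mixed model meets every word of that description, and so may a model with a facility intercept only, yet neither protects the stated contrast.

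Two related matters carry little weight here. The completion logit has no arm effect, so the error rates above do not apply to it; clustering there is a minor secondary point. Facilities also differ for non-random reasons, but that is confounding, which no random-effects structure removes.

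**Conclusion.** The concern holds as a conditional one. The stated primary analysis carries no named allowance for the unit of allocation, although the design and sample size rest on it. If the model is fitted with patient random effects only, two-sided type I error is about 0.11 when the planning design effect of 1.5 applies to the change contrast. At the implied ICC of 0.0102 and an assumed individual autocorrelation of 0.5, it lies between 0.05 and about 0.165, depending on how stable facility effects are across visits. Higher individual autocorrelation or a higher ICC would raise the upper end. The document fixes none of these correlations, so an unconditional statement that the error doubles is not supported. The gap should be closed before analysis, because following the text as written can produce intervals that are too narrow.

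**What to change.** State the random-effects structure of the primary model: patient, facility and facility-by-visit, with Kenward-Roger or Satterthwaite degrees of freedom. An acceptable alternative is a two-stage analysis of facility-level mean changes, adjusted for covariates at the first stage, on t with about 8 degrees of freedom. For the generalised mixed models, name a cluster method with a small-sample correction. As a lesser matter, account for facility in the completion model.

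The change is to wording only. The price is wider intervals: about 1.22 times for clustering at a design effect of 1.5, and 1.18 times for the t quantile, together 1.22 × 1.18 = 1.44 times those of a patient-level analysis. If facility effects prove stable over time, the first factor shrinks towards 1. The sample size already covers the first factor but not the second. On the planning proportions with 250/1.5 = 166.7 effective patients per arm, power falls from about 79% under the normal approximation to about 69% on t with 8 degrees of freedom. Handling of confounding from non-random allocation needs its own provision.

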**Methods:**

A multicentric hybrid Type I mixed method implementation research design will be used to adapt and evaluate the implementation feasibility and effectiveness of delivering a self-efficacy-based intervention under National Tuberculosis Elimination Program (NTEP) settings in India. A two-arm non-randomized cluster intervention design will be employed to evaluate the impact of a self-efficacy intervention, which includes individual counseling and peer group sessions (*n* = 240) in comparison to the standard of care (*n* = 240) on primary and secondary outcomes. Qualitative in-depth interviews and focus group discussions, guided by the Consolidated Framework for Implementation Research (CFIR), will be conducted to explore contextual factors influencing implementation.

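### Covariates chosen by observed baseline difference and, as the text reads, entered as main effects would leave confounders of change uncontrolled in this non-randomised comparison

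*Protocol article*

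**What the plan says.** All references are to the protocol article.

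- **Design** (Design for primary objective 2): "A two-arm, non-randomized cluster intervention study will be conducted to achieve this objective". Sample size gives five clusters per arm.
- **Model** (Analysis of study outcomes data): continuous outcomes go into linear mixed models. The fixed effects are arm, time and their product. Baseline is one of the outcome visits: "Time (0 = baseline, 1 = 3 months post-baseline; 2 = 6 months post-baseline". The only interaction listed is "Interaction terms between the treatment arm and time (Treatment × Time interaction term".
- **Effect** (same section): "This modeling approach will allow estimation of mean differences in change scores between study arms".
- **Covariates** (same section): "Covariates showing meaningful baseline differences will be adjusted for in the models". No covariate is named.
- **Other control of confounding** (Sample size, text after Figure 1): "the matching of average self-efficacy scores between the intervention and control clusters will be assessed".
- **Other interactions** (Mediator/moderator analysis): further interaction terms are added to the models already specified, to study moderation.
- **Outcomes without a baseline value** (Analysis of study outcomes data): adherence and treatment outcome are assessed at midline and endline only.

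**The concern.** There are two linked problems.

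The first is the selection rule. A covariate confounds the comparison through two things together: its imbalance between arms and its effect on the outcome. The rule looks only at the first, after the data are in. A strong predictor of change with modest imbalance can be left out, while a weak predictor with a visible imbalance is let in.

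The second is that the adjustment may not reach the effect. A characteristic fixed at baseline and entered as a main effect moves all three visits by the same amount. The treatment effect is a difference between visits, so that amount drops out. Readers would then be given an adjusted estimate that is in practice the unadjusted one.

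With ten facilities allocated without randomisation, arms may differ in TB type (drug-sensitive or drug-resistant), depression, alcohol use or age. If such factors affect how fast self-efficacy improves, the difference would be credited to the intervention or would mask its effect.

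**Working it through.** The plan gives no figure for confounding, so there is none to reproduce. Its benchmark is d > 0.3 (Hypothesis/research question). Dropout of 10% and ten clusters come from Sample size, and 240 per arm from the Abstract. All other inputs below are assumptions.

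**Step 1: algebra.** Let x be a baseline covariate entered as a main effect:

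E[Y at visit t] = α + β·arm + γ_t + δ_t·arm + θ·x, with γ_0 = δ_0 = 0.

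Month 6 minus baseline is γ_2 + δ_2·arm. The term θ·x is gone. If x in truth also changes the 6-month gain by λ per unit, the arm-by-time estimate carries a bias of λ × (mean of x in intervention − mean of x in control), whether or not θ·x is in the model.

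**Step 2: simulation with complete data.** There were 60 simulated trials of 500 patients in ten clusters at three visits, with no true intervention effect. A binary covariate had prevalence 60% against 30% and added 3 points to the 6-month gain. Expected bias: 3 × (0.6 − 0.3) = 0.9 points. The mixed models used a patient random intercept.

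| Analysis | Mean 6-month effect (truth 0) |
|---|---|
| Arm-by-time, no covariate | 0.791 |
| Plus covariate main effect | 0.791 (largest difference from the row above 1e-12) |
| Plus covariate-by-time terms | −0.128 |
| 6-month score on baseline score, arm and covariate | −0.090 |

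The covariate-by-time terms move the estimate by 0.791 − (−0.128) = 0.919, which matches the expected 0.9. The last two rows are zero within simulation error.

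**Step 3: with dropout at month 6.**

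| Loss | No covariate | Main effect | Mean shift | Largest shift |
|---|---|---|---|---|
| 10%, at random | 0.7903 | 0.7918 | 0.0015 | 0.06 |
| 10%, dependent on x | 0.7786 | 0.7891 | 0.0105 | 0.07 |
| 30%, dependent on x | 0.6511 | 0.7048 | 0.0537 | 0.14 |

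At the planned 10%, the main effect changes a bias of about 0.8 points by roughly 0.01 at most on average.

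**Step 4: size on the SD scale.** Bias = imbalance (SD) × effect on change (SD per SD):

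- 0.15 × 0.15 = 0.0225 SD, or 0.0225/0.3 = 7.5% of the threshold
- 0.15 × 0.3 = 0.045 SD, or 15%
- 0.3 × 0.3 = 0.09 SD, or 30%

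This is for one covariate. Biases from independent covariates add, with their signs.

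**Step 5: what selection by imbalance catches.** With 240 per arm and clustering ignored, the standard error of a standardised difference is √(2/240) = 0.0913. Take a true imbalance of 0.15 SD and two possible meanings of the rule, neither stated in the plan:

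- flag at p < 0.05: 0.15/0.0913 = 1.64, so the chance is Φ(1.64 − 1.96) ≈ 38%
- flag at an observed difference above 0.1 SD: (0.15 − 0.1)/0.0913 = 0.55, so the chance is Φ(0.55) ≈ 71%

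Under either, whether the covariate is used depends partly on chance and not at all on its prognostic strength.

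**The case against.** The strongest reply is that the article does not say how covariates enter. It says that they will be adjusted for, and an analysis plan that is not shown could specify covariate-by-time terms, which would give real adjustment. That stands, and it makes the cancellation conditional. Main effects remain the natural reading, because arm-by-time is the only interaction in the model list and further interactions appear only for moderation. The selection rule is stated outright, and the objection to it holds however covariates enter.

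Four stronger readings are tempting, and the document does not support them.

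- A reader might infer that the whole comparison stays unadjusted. It does not. A change contrast already removes constant level differences between arms. Adherence and treatment outcome have no baseline value, so main effects do adjust those. For non-normal outcomes modelled with other link functions, the cancellation is only approximate.
- A reader might infer screening at p < 0.05. The plan sets no such test, so the 38% above is only an illustration. Even at p < 0.05, a 0.3 SD imbalance would be flagged about 91% of the time.
- A reader might infer that the bias figures predict this trial. They follow from the assumed inputs and show a mechanism.
- A reader might infer that the check of mean self-efficacy between clusters is blinded by the eligibility cut-off of 30. The text does not limit that check to enrolled patients. With illustrative inputs (screened means 30 and 36, SD 10), a gap of about 1.8 points would still show among those enrolled.

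**Conclusion.** The concern holds in a bounded form. Selecting covariates by observed baseline difference is a poor rule for a non-randomised five-against-five cluster study, because it is data-driven and ignores prognostic strength. If the covariates enter only as main effects, they leave the linear-model change contrast unchanged with complete data and virtually unchanged at 10% dropout. Confounders of change in self-efficacy, and in the other continuous outcomes measured at baseline, are then uncontrolled.

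The size cannot be fixed from the document. Under the assumptions shown, one covariate contributes about 0.02 to 0.09 SD against the 0.3 threshold. The conclusion rests on an identity-link model and on the main-effects reading. The criticism of the selection rule rests on neither.

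**What to change.** Replace the baseline-difference rule with a covariate set named in advance on prognostic grounds: TB type (drug-sensitive or drug-resistant), age, sex, baseline PHQ-9 and baseline AUDIT-C. Include district only if it can be estimated with ten clusters in three districts. Use baseline values only, since depression and alcohol use are also studied as mediators.

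Then choose one primary model in advance:

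- 3- and 6-month scores as outcomes, with baseline score and these covariates as predictors; or
- the change model as written, with a covariate-by-time term for each covariate.

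Report the other as a sensitivity analysis. In groups that differ at baseline the two can give different answers, so the choice should not be left until the data are seen.

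The cost is a change of wording and a few extra parameters. No new data, sample size change or recruitment change is needed.
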